#### **Exclusion criteria**

- Emergency operation
- Medically unstable or severe comorbidities that contraindicate exercise (e.g., unstable cardiovascular disease).
- Impaired cognition or confusion
- Impaired vision, cognition or physical impairment (UL and LL) in functional task components

## **Study Design**

This study is a randomized control trial, and a double-blinded assessor (blinding of patients and assessors and intention to treat analysis). The study will be carried out at the Hospital Canselor Tuanku

Mukhriz (HCTM), Cheras, Kuala Lumpur, Malaysia. Participants will be recruited from the surgery and anaesthetic clinic at the HCTM. Randomization of participants by using a computer-generated random number sequence (Block Randomization), will allocate each participant to either an intervention group or standard care group (1- 70).

## **Blinding and allocation**

Patients and outcome assessors, will remain blinded to treatment allocation. However, the treating physiotherapists cannot be blinded due to the nature of the intervention. To maintain blinding, details of the intervention will not be recorded in the medical records. Outcome assessments will be conducted by a blinded assessor based off-site from the outpatient department, ensuring impartiality in both inpatient and outpatient settings. Intervention sessions will occur on different days from those scheduled for outcome assessments to further reduce the risk of unblinding. If a participant from the intervention group discloses details of their intervention to the assessor, this will be documented and reported, with the rationale recorded. All analyses will be performed on an intention-to-treat basis once randomization is unblinded.

Following recruitment and baseline assessments, participants will be randomly assigned to one of two groups which will be control group (MICT) or the intervention group (HIIT) using a computer-generated random number sequence. Allocation will be conducted by an independent individual utilizing a block randomization method (5 blocks of 14). An administrative assistant, independent of the trial, will prepare 70 sequentially numbered opaque envelopes, each containing a group allocation. A physiotherapist, trained in the study protocol, will deliver the intervention. Participants in the control group will receive moderate-intensity continuous training (MICT), while those in the intervention group will engage in high-intensity interval training (HIIT) preoperatively. Both groups will commence and conclude sessions with a warm-up and cool down to mitigate the risk of adverse events.

This study is will be conducted at a teaching hospital of the Hospital Canselor Tuanku Muhriz, Malaysia. Prospective consecutive patients will be invited to participate in the study prior to elective major abdominal surgery from February 2025 to July 2026. Fig 2 summarises the design of the trial, and each of the trial's aspect is described in detail below.

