## **2.0 Research Methodology**

### **2.1 Study Design**

This study will be 2 phases: (i) Phase 1 will be a cross-sectional web survey will be conducted to explore the current practice amongst physiotherapists treating patients following major abdominal surgery in Malaysia hospitals and (ii) Phase 2 will be a prospective, double-blinded randomized controlled trial which aims to determine the effect of HIIT over MICT on multi-domain recovery.

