## **Study Method**

### **Intervention care group (HIIT)**

Participants in the intervention group will receive the same care as the standard care group. Additionally, for aerobic exercise this will be a moderate intensity which is 55-75% of maximum heart rate (MHR) in week one, with graduation to high intensity in week two on > 80% of MHR [24]. Aerobic exercise training (eg: Treadmill, Cycle ergometer, body weight exercises) 1-3 times per week (30 minutes) for an overall duration typically 2-4 weeks prior to the date of surgery. Patients' Maximum Heart rate ( $210 - \text{age}$ ) and Karvonen Formula will be used for the targeted heart rate. Patients' heart rate will be monitored along the aerobic training using a smartwatch. However, those patients who are on beta-blockers or with underlying cardiac conditions, training intensity will be guided by the Rating of Perceived Exertion (RPE) between 16-18 RPE score, with appropriate adjustments made to ensure safety. The interval training will be 30-60 seconds of high-intensity training with 1- 2 minutes of active recovery (light activity or complete rest) between intervals to facilitate recovery. This will be repeated for a total of 5-10 cycles [32].

In addition to aerobic training, participants will receive the same progressive resistance exercise and inspiratory muscle training, with intensity matched to that of the standard care of

MICT group. Aim for a total session duration of about 20-30 minutes, including warm-up and cool-down. This includes 10-15 minutes of HIIT, depending on the patient's tolerance. Sessions will be done 1-3 times per week, with rest days in between to allow for recovery. Participants will also receive an illustrated handout to guide continued training support by caregivers, including recommendations on maintaining a standard amount of aerobic and strength exercise per week. A detailed session attendance checklist and vital signs will be recorded at each session to monitor adherence.

All other aspects of patient care such as preoperative management, general anaesthesia, intraoperative ventilation settings, fluid administration, prophylactic antibiotic use, pain management, management of lines and drains, general nursing care, and discharge planning will be administered at the discretion of nurses and physicians in accordance with routine clinical practices at hospital for both groups.

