### **Standard Care for Control Group (MICT)**

This will be a tailored and supervised by a single physiotherapist (more than 10 years clinical experiences in cardiorespiratory) in outpatient hospital setting. Participants will engage in an aerobic (moderate intensity continuous training), strengthening exercise and inspiratory muscles training program prior to the date of their surgery.

For aerobic exercise this will be a low intensity in week one with graduation to moderate intensity. Moderate intensity continuous training (MICT) will allow 55-75% of maximum heart rate (MHR) [33]. Aerobic exercise training (eg: treadmill, cycling, walking exercise) 1-3 times per week (60 minutes) for overall duration typical 2-4 week prior to date of surgery. Patients' Maximum Heart rate (210-age) and Karvonen Formula will be used for targeted heart rate. Patients' heart rate will be monitored along the aerobic training using smart watch. However, the Karvonen formula may not be suitable for all patient populations, particularly those on beta-blockers or with underlying cardiac conditions. In such cases, training intensity will be guided the RPE between 10-13 RPE score, and appropriate modifications will be made to ensure safety. This approach allows for individualized intensity adjustment while maintaining the safety and effectiveness of the intervention.

For the progressive resistance exercise, the following muscle groups will be targeted: biceps brachii, triceps brachii, pectoralis major and minor, latissimus dorsi, deltoid and rhomboids using free weights. The intensity will be 70-80% of estimated 10 repetitions

maximum. The load not provided joint pain or severe muscle fatigue and/or arm fatigue on RPE of 10-13 on 6-20 RPE score [60]. Aim for a total session duration of about 45-60 minutes, including warm-up and cool-down. This includes 30-45 minutes of MICT, depending on the patient's tolerance. Sessions will be done 1-3 times per week [60].

In addition to the PVC weighted bar, we also used different types of resistance training such as band, dumbbells, kettlebells. Inspiratory muscles training will be given 20 mins per day with 30% of maximum inspiratory pressure (MIP) [14].

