#### **3.2 Informed consent**

If a patient meets the above inclusion criteria, they will be invited to participate in the study by the researcher team who will provide them with an information sheet detailing the study aims and time commitments. Once a potential participant provides informed consent, they will be enrolled to participate in the study. Participants can choose to withdraw at any time.

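### The trial is at most assessor-blinded: patients carry out visibly different programmes, so the double-blind label is wrong and the self-reported outcomes are rated unblinded

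*Protocol*

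**What the plan says.** Section 2.1 describes Phase 2 as a "prospective, double-blinded randomized controlled trial", and the Abstract (Methods) uses the same label. The Phase 2 section Study Design spells out who is meant: "blinding of patients and assessors and intention to treat analysis". Blinding and allocation repeats it as a plain commitment: "Patients and outcome assessors, will remain blinded to treatment allocation". It makes one exception: "the treating physiotherapists cannot be blinded due to the nature of the intervention".

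That section then lists the means of keeping the blind. Intervention details stay out of the medical records, the assessor is based off-site, and training sessions and assessments fall on different days. If a participant in the intervention group tells the assessor what they have been doing, this is documented. Under Data collection, the blinded outcome assessors also administer the questionnaires face to face.

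**The concern.** Blinding to allocation means not knowing which of the two programmes one has been assigned to. In an exercise trial the patient performs the programme, so the claim is credible only if the two programmes look and feel alike or if something is done to disguise the difference. Neither is apparent here.

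At stake is how the results may be read. For a questionnaire the patient completes about their own state, the patient is the outcome rater. If the patient knows the allocation, that outcome is unblinded, whoever administers the form. A reader told that the trial is double-blind would credit the comparisons of anxiety, fatigue, quality of life, perceived capacity and perceived change with a protection they do not have.

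**Working it through.** No formula applies. The check sets the programmes side by side, sorts the safeguards by whom they protect, and counts the outcomes affected.

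**1. Can patients tell the programmes apart?** Inputs are the two intervention sections and Table 2.

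| Feature | HIIT | MICT |
|---|---|---|
| Format | bursts of 30-60 s, recovery of 1-2 min, 5-10 cycles | continuous |
| Heart rate (Table 2, share of peak) | above 80% | 55-75% |
| Borg RPE (Table 2) | 16-18 | 10-13 |
| Borg dyspnoea (Table 2) | 5-8 | 3-4 |
| Talk test (Table 2) | speech broken by breaths | full sentences |

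The RPE bands do not overlap, and neither do the dyspnoea bands. Format alone identifies the programme to the person doing it. Session length points the same way: "Aim for a total session duration of about 20-30 minutes, including warm-up and cool-down" for HIIT against "Aim for a total session duration of about 45-60 minutes, including warm-up and cool-down" for MICT. The Abstract, however, gives one-hour sessions without separating the arms, so the point is not rested on duration.

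**2. Whom do the safeguards protect?**

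- No intervention details in the medical records: the assessor.
- Assessor based off-site: the assessor.
- Sessions and assessments on different days: the assessor.
- Documenting disclosure by a participant: the assessor.

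That is four of four for the assessor and none for the patient. No sham and no procedure for disguising the allocation is described.

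**3. Which outcomes are rated by the patient?** The Secondary outcome measures section and the bio-impedance entry that follows it describe nine outcomes, and the schedule in Fig. 1 lists the same nine.

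- Self-reported: HADS, EQ-5D-5L, SAQ, FSS, Global Rating of Change = 5.
- Performance or device measures: 1-minute sit-to-stand, SPPB, hand grip, bio-impedance = 4.
- 5 + 4 = 9, so 5 of 9 are self-reported.

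The count depends on the list used. Statistical analysis omits HADS: 5 - 1 = 4 self-reported out of 9 - 1 = 8. Secondary objective (i) in section 1.3 omits SAQ and Global Rating of Change: 5 - 2 = 3 out of 9 - 2 = 7. On every list the affected share is between 3/7 (43%) and 5/9 (56%).

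Baseline values are not affected, because Blinding and allocation places randomisation after the baseline assessments.

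**The case against.** The best defence is that both arms are active, supervised exercise. Patients could know what they do without knowing which programme is the experimental one, and expectation could then favour either arm or largely cancel. In week one the HIIT arm also trains at 55-75% of maximum heart rate, which is the MICT range. This has force against any claim about how large the bias is. It does not rescue the text, which claims blinding to allocation, describes no concealment of either kind, and moves the HIIT arm to high intensity from week two.

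Three stronger readings are tempting and should not be adopted.

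- *That patients also know the hypothesis.* Section 3.2 promises an "information sheet detailing the study aims and time commitments", and a reader might infer that it reveals which arm is favoured. The consent pages are not available, and an aim can be worded as a neutral comparison of two programmes. This cannot be checked.
- *That the disclosure rule proves patients know their allocation.* It shows that patients can describe what they did, which fits the point. It does not show that they know which arm is experimental.
- *That the bias can be put in metres on the walk test.* One could multiply the protocol's SD of 101.6 m by an assumed expectation shift and compare the result with the 29.4 m planning difference. The documents give neither the size nor the direction of such a shift, and 6MWT is not a self-report. Both primary outcomes depend on effort, but they are measured by a blinded assessor. The walk test allows no extra encouragement, and MIP requires three readings with a coefficient of variation below 10%.

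It is also fair to say that no sentence labels an individual questionnaire as blinded. That impression comes from the blanket statements.

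**Conclusion.** The statement that patients are blinded to allocation is wrong as written. The protocol's own description of the two programmes contradicts it, and every listed safeguard serves the assessor. The trial is at most assessor-blinded.

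The reach is the five self-reported secondary outcomes (5 of 9 as described and scheduled; 4 of 8 in the analysis list). No number can be attached to the bias, and none is needed. The conclusion rests only on the difference in format and exertion in the intervention sections and Table 2, and on the absence of any described means of disguising it. It does not depend on the content of the information sheet, on session length, or on the sample-size figures. No estimate, test or sample size changes. What changes is how firmly the self-reported comparisons may be interpreted.

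**What to change.** - In the Abstract (Methods), section 2.1 and the Phase 2 Study Design section, replace the double-blind and patient-blinding wording with 'assessor-blinded'.
- In Blinding and allocation, rewrite the opening statement to say that outcome assessors are blinded, while patients and treating physiotherapists are not.
- Add one sentence, for example in Statistical analysis, saying that HADS, EQ-5D-5L, SAQ, FSS and Global Rating of Change are rated by unblinded patients and that conclusions on them are open to expectation bias.

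Optionally, the assessor could record a guess at the allocation, as a check on the one blind the trial has. Guesses made after outcomes have been seen can partly reflect those outcomes, so this is not essential.

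The cost is wording in four places and one added sentence. The stated design becomes slightly less favourable; treatment, schedule, sample size and analysis are unchanged.

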## **Sampling and Size Calculation**

The sample size was calculated based on the primary outcome measure (6MWT). A recent systematic review of prehabilitation in patients undergoing major abdominal surgery reported significant improvement in 6MWT, with a mean difference of 29.4 meters (95% CI: 5.6 to 53.3 meters;  $p = 0.02$ ) compared to standard care [31]. The estimated standard deviation was approximately 101.6 meters, corresponding to an effect size (Cohen's  $d$ ) of 0.29. Using this effect size, with  $\alpha$  of 0.05 and power of 80%, the required sample size was calculated to be 54 participants. Allowing for a 30% dropout rate, a total of 70 participants (35 per group) will be recruited. Sample size calculation was performed using G\*Power version 3.1.9.7.

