#### **3.3 Data Management and Quality**

Data will be managed using an Excel database and SPSS version 27.0. Thorough training will be provided to all personnel involved in data collection, entry, and verification to ensure accuracy and consistency across measurements and to identify missing data. Regular checks will be performed to detect any inconsistencies within and between datasets. Data entry, security, and storage will follow strict protocols to ensure quality and confidentiality. All data will be encrypted and stored in a password-protected system with limited access, complying with privacy regulations. Additionally, two independent clinical members will serve in an advisory role to the clinical investigators, overseeing participant withdrawals, monitoring ethical conduct, and reviewing any serious adverse events.

Access to the final trial dataset will be limited to the principal investigator and designated members of the research team. There are no contractual agreements restricting the investigators' access to the data, and neither the sponsor nor the funder will have access to the raw dataset. This ensures the research team's full independence in data management, analysis, and reporting. The complete trial protocol is publicly available via the ANZCTR registry, and the raw dataset will be made available upon reasonable request and approval by the principal investigator. Process evaluation findings will be published in peer-reviewed journals and presented at relevant academic conferences.

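### The protocol publishes a fixed block scheme (5 blocks of 14), so anyone tracking allocations could know about one in eight in advance; this is an avoidable risk of selection bias, not a shown bias

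*Protocol*

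**What the plan says.** All of this is in the protocol.

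- **Sequence.** Blinding and allocation: "Allocation will be conducted by an independent individual utilizing a block randomization method (5 blocks of 14". No varying block size and no stratification factor is named there or under Study Design.
- **Concealment.** An assistant independent of the trial "will prepare 70 sequentially numbered opaque envelopes, each containing a group allocation".
- **Size.** Sampling and Size Calculation: "a total of 70 participants (35 per group) will be recruited".
- **Who knows the arm.** Blinding and allocation: "the treating physiotherapists cannot be blinded due to the nature of the intervention". The control-arm section says care is "supervised by a single physiotherapist", and the HIIT section says "Participants in the intervention group will receive the same care as the standard care group".
- **Publicity.** Section 3.3: "The complete trial protocol is publicly available via the ANZCTR registry".
- **Entry of patients.** Section 3.2 has the research team invite patients. Blinding and allocation says invitation is consecutive and that assignment follows recruitment and baseline assessment. No section says who opens the envelopes, or whether the treating physiotherapist takes any part in invitation or screening.

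**The concern.** Opaque numbered envelopes hide what is in the next envelope. They do not hide what a known block forces it to contain. Once seven patients in a block have gone to one arm, every remaining place in that block belongs to the other. The block length is printed in a public document, and at least one unblinded person at the single site treats patients as they are allocated, so a running tally is feasible.

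The possible harm is selection bias. Eligibility involves judgement, since the exclusion criteria include comorbidity severe enough to contraindicate exercise. If the person making that judgement, or deciding when to invite, could foresee the arm, fitter or frailer patients could be entered selectively, even without intent. Blinded outcome assessment and intention-to-treat analysis act after entry and do not undo this.

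**Working it through.** **Inputs.** Five blocks of 14 and 70 envelopes (Blinding and allocation); 35 per group (Sampling and Size Calculation). The 7:7 split within a block is inferred from 35/5 = 7; the protocol does not state it.

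**Step 1: the plan's own figures.** 5 × 14 = 70 and 5 × 7 = 35 per arm. The scheme fits the sample size exactly.

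**Step 2: assignments known with certainty.** In a balanced block of 2m, an assignment is certain once the other arm's m places are used. The expected number per block is 2m/(m+1), so the share is 1/(m+1).

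- m = 7: 14/8 = 1.75 per block, a share of 12.5%. Over five blocks, 5 × 1.75 = 8.75 of 70.
- A simulation of 200,000 blocks gave a share of 12.52%.
- The last place in every block is always certain, so at least 5 of 70 are. The number certain at the end of a block is 1 with probability 0.538, 2 with 0.269, 3 with 0.122, and 4 or more with 0.070.

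**Step 3: correct guesses.** Guessing the arm that is behind gains (4^m/C(2m,m) − 1)/2 correct guesses per block over chance.

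- m = 7: (16384/3432 − 1)/2 = 1.887. Over five blocks this is 9.43, so 35 + 9.43 = 44.4 of 70, or 63%.

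**Step 4: alternatives under the same formulas.**

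| Sequence | Certain | Correct guesses |
|---|---|---|
| Five blocks of 14 | 8.75 of 70 | 63% |
| One list of 70, 35:35 | 70/36 = 1.94 of 70 | (35 + 4.76)/70 = 57% |
| Last 28 as two blocks of 14 | 2 × 1.75 = 3.5 of 28 | 63% |
| Last 28 as one list, 14:14 | 28/15 = 1.87 of 28 | (14 + 2.85)/28 = 60% |
| Last 14 as one list, 7:7 | 1.75 of 14 | 63% |

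The rows for 28 and 14 assume that earlier blocks are complete, so the places left are balanced. A single list for the last 14 is the same thing as the last block, so nothing is gained.

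Smaller fixed blocks would be worse: the certain share is 1/3 for blocks of 4 and 1/4 for blocks of 6. In simulation, random sizes 4, 6 and 8 cut the certain share to about 2.4% but raised tally guessing to about 68%. Random sizes 10, 14 and 18 left tally guessing at about 63%; their benefit lies mainly in removing the certain assignments.

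**The case against.** The strongest reply is that the protocol already separates the key steps. An independent person generates the list, an assistant outside the trial fills the envelopes, patients are invited consecutively, and assignment comes after eligibility, consent and baseline. Nothing says the treating physiotherapist invites, screens or opens envelopes. The mention of a single physiotherapist is in the control-arm section only, and Blinding and allocation also uses the plural. A therapist sees attendance rather than envelope order, and a patient who withdraws before the first session could break the tally. Fourteen is also already a large block.

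Most of this stands. It means that the 12.5% describes what a complete tracker could know, not what anyone will know. It does not remove the predictability, because neither an independent list-maker nor a sealed envelope changes what a published block forces. Consecutive invitation still leaves judgement about eligibility.

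A reader might go further and infer a bias of several metres in the 6MWT. If patients better by x m were entered at every HIIT guess and worse by x m at every MICT guess, the arms would differ by 2 × 9.43/35 = 0.54x: about 5 m for x = 10 and 13 m for x = 25, against the planning difference of 29.4 m. The documents do not support that reading. The value of x is an assumption with no source in the protocol, and the calculation needs perfect tallying and steering at every untied entry, so it is a worst case. It is also a shift in level. Baseline 6MWT and MIP are measured before assignment, and the Statistical analysis section makes the time-by-group interaction the test of whether the intervention works; a constant shift cancels from it. The shift would remain in the group main effect, and the interaction would not remove differences in how patients recover.

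**Conclusion.** The point holds as a weakness of design that is cheap to reduce. With known 7:7 blocks of 14, a person who tracks all earlier allocations in the block could be certain of 8.75 of 70 assignments on average (12.5%) and guess about 63% correctly, against 50% by chance. This rests on the inferred 7:7 balance and on complete tracking.

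It is a risk of selection bias, not evidence of one. It becomes real only if the knowledge reaches those who invite or screen, and the protocol is silent on that. Neither a conclusion that allocation has been subverted nor any figure in metres for the effect on the 6MWT follows from the text.

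**What to change.** 1. Remove the fixed block size. For envelopes not yet used, the same independent person generates a new sequence and the assistant refills the same numbered envelopes; envelopes already issued stand. Preferably use one permuted list for the remaining places, ending at 35:35. Otherwise use large block sizes varied at random (for example 10, 14 and 18). Do not move to small blocks.
2. Keep the sizes and the list in a restricted document, away from recruiting and treating staff and out of the public protocol.
3. State that the treating physiotherapist takes no part in invitation or the eligibility decision.

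The gain from step 1 depends on progress, and the protocol's recruitment window runs from February 2025 to July 2026. From patient 1, a single list would cut certain assignments to about 1.9 and correct guesses to 57%. With 28 envelopes left, correct guesses fall only to about 60%. With 14 or fewer left, a single balanced list brings nothing, and only steps 2 and 3 help.

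The cost is a new list and a few sentences, with no extra patients or staff. There are three downsides. Imbalance during enrolment is larger for a time: for a full list of 70 the SD of the arm difference at the midpoint is 2 × √(35 × 0.25 × 35/69) = 4.2 patients. Final balance is reached only if all 70 are enrolled. The change also needs an amendment approved by the ethics committee.
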